**1-year visit**
• Same as 6-month visit except no blood sampling
• A venous ultrasound is performed to assess reflux
**18-month visit**
• Same as 6-month visit except no blood sampling
**2-year visit**
• The nurse completes the follow-up form
• The patient self-completes the QOL form
• Bleeding/Other Serious Adverse Event form is completed
• The success of blinding (patient, nurse, and investigator) is assessed (or at Study Termination if earlier than 2 years).

### Primary and secondary outcome measures

The primary outcome measure is the incidence of PTS during 2 year follow up. PTS will be diagnosed at the 6 month visit or later if the patient reports pain and swelling of ≥ 1 month's duration that is typical in character (worse at the end of the day or with prolonged sitting or standing, and better after a night's rest and leg elevation), and that is present ≥ 6 months after the acute DVT [52]. Patients diagnosed with PTS will be considered to have reached the study endpoint. Severity of PTS will be graded according to the Villalta scale [53], a clinical post-thrombotic syndrome measure that rates the severity of five patient-rated symptoms and six clinician-rated clinical signs [53]. A Villalta score of 5–9 represents mild post-thrombotic syndrome; 10–14, moderate post-thrombotic syndrome; and > 15 or presence of a venous ulcer, severe post-thrombotic syndrome [53].

Secondary outcomes measures include:

• Reflux: Reflux will be assessed and quantified in a standardized fashion by venous ultrasound [52,56].

• Recurrent VTE: Objective tests and validated algorithms will be used to diagnose recurrent DVT and PE, as described previously [57-59], and all events and deaths will be independently and blindly adjudicated. Death from VTE will be assessed as 'likely' or 'unlikely' after review of the death certificate, patient chart, autopsy report (where available) and by contacting the treating physician.

• Bleeding: Clinically suspected bleeding events will be documented by recording the clinical event and results of any objective diagnostic testing performed. Bleeding will be defined as major if it is clinically overt and associated with a fall in hemoglobin of 20 g/L or a need for transfusion of ≥ 2 units of red blood cells; if it was intracranial or retroperitoneal; or if it warranted the permanent discontinuation of anticoagulation. Less severe clinically overt bleeding which is considered abnormal will be classified as minor.

• Markers of inflammation: C-reactive protein will be assayed using a nephelometric assay. IL-6, IL-8 and MCP-1 will be measured using commercial ELISA kits which include plasma controls (Biosource Europe SA, Nivelles, Belgium). At the time of blood draw for markers of inflammation, data will be recorded on time of day, type and duration of heparin use, concomitant medications and medical conditions.

• DNA polymorphisms associated with thrombophilia: QIAGEN kits and standard protocols will be used to extract DNA from peripheral blood leukocytes. Samples will be run on the ABI Prism 3100 Genetic Analyzer to analyze Factor V Leiden, Prothrombin G20210A, PAI-1 4G/4G, TAFI T1053C, TFPI C536T, TFPI T33C and FXIII Val34Leu.

• Coagulation and ELISA-based assays: Factor VIII assays will be performed using the PTT based Diagnostica Stago (Abbott Diagnostics Canada, Mississauga). D-dimer testing will be performed with the IL-Test Latex Agglutination method (Instrumentation Laboratory, Lexington, USA). Lupus anticoagulant testing will be performed on an ACL9000 (Instrumentation Laboratory, Lexington, USA). Standard aPTTs are performed using Alexin HS (Trinity Biotech USA, St. Louis, USA) and HemosIL APTT-SP (Instrumentation Laboratory, Lexington, USA) as a screening test. Abnormal results are followed by a 50:50 mix using Cryocheck Normal (Precision Biologic, Dartmouth, NS), followed by Platelet Neutralization Procedure. Additionally, a Dilute Russell Viper Venom test is performed using IL test LAC Screen followed by Confirm (Instrumentation Laboratory, Lexington, MA, USA). IgG and IgM antiphospholipid antibodies are tested usingapHL-HRP ELISA Kit (Louisville APL Diagnostics, Doraville, USA).

• Quality of life measures: Quality of life will be measured using the SF-36 questionnaire for generic QOL [60,61]., and the VEINES-QOL/Sym questionnaire for venous disease-specific quality of life, which our group developed and validated [62,63]

• Cost Effectiveness measures: A decision tree-based cost effectiveness analysis will be used to assess the relative cost-effectiveness of the active stockings in reducing the incidence of PTS, as compared to a strategy of inactive stockings [64,65]. Tree structure will schematically reflect the clinical trajectory for each strategy [66]. Sensitivity analyses will be conducted to verify the robustness of the qualitative conclusions to variations in the data [67].

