For the secondary outcomes valvular reflux, recurrent VTE, death from VTE, venous ulcer, major bleeding, and severity of PTS, rates in the two intervention groups will be described, and between-group differences explored in similar regression procedures. For differences in mean quality of life scores between intervention groups, analysis of variance incorporating treatment and center will be used. A difference of 4–5 points between groups is considered to be clinically meaningful. Analysis of covariance with adjustment for age, sex and comorbidity will also be used to compare quality of life between groups. For the biomarker variables, univariate analysis will be used to determine the strength of association between each biomarker variable and the occurrence of PTS. For genetic markers, heterozygotes and homozygotes will be analyzed together, given the rarity of homozygotes. IgG, IgM and lupus anticoagulant results will be dichotomized as normal or abnormal. Factor VIII, D-dimer and markers of inflammation will be analyzed both as continuous data and as proportion of values exceeding the upper 90^th ^percentile. For binary and nominal data, the appropriate chi-square tests will be used to examine the respective crude associations, and for continuous variables, the unpaired 2-tailed t-test. To examine adjusted associations, multiple logistic regression analyses will be performed in which the dependent variable is the presence of PTS. The independent variables to be tested are markers of thrombophilia, D-dimer, and levels of CRP, IL-6, IL-8 and MCP-1. Other variables of interest (for interaction and/or confounding) are age, sex, ethnicity, comorbid illness, allocation to active ECS, type and duration of heparin and warfarin use, type of DVT (unprovoked vs. secondary; anatomic extent of DVT), and recurrent DVT during follow-up. The analyses will aim to (1) identify the strength of the association between relevant biomarkers, other relevant explanatory variables and PTS; and (2) explore relevant interactions. Similarly, multiple linear regression will be performed in which the dependent variable is the severity of PTS, as measured by the Villalta scale.

An interim analysis for efficacy will be performed when half of the subjects have completed 2 years of follow-up. The analysis plans call for a Lan-DeMets alpha spending approach with an O'Brien Fleming boundary [70].

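### The Villalta severity bands give no grade to a score of exactly 15, or to a diagnosed PTS case scoring below 5, so the grades need not sum to the primary PTS count

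*Protocol article*

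**What the plan says.** All the definitions stand in the protocol article under *Primary and secondary outcome measures*.

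- **Diagnosis (primary outcome).** "PTS will be diagnosed at the 6 month visit or later if the patient reports pain and swelling of ≥ 1 month's duration", with a typical pattern and still present at least 6 months after the acute DVT. No Villalta score enters this rule.
- **Severity.** "Severity of PTS will be graded according to the Villalta scale", an instrument that "rates the severity of five patient-rated symptoms and six clinician-rated clinical signs".
- **Bands.** "A Villalta score of 5–9 represents mild post-thrombotic syndrome; 10–14, moderate post-thrombotic syndrome"; and "> 15 or presence of a venous ulcer, severe post-thrombotic syndrome".

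Under *Aims of the study*, reducing severity is the first secondary aim. Under *Statistical analysis*, the plan for a list of secondary outcomes ends: "severity of PTS, rates in the two intervention groups will be described, and between-group differences explored in similar regression procedures". The same section opens by applying intention-to-treat to every outcome.

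**The concern.** A graded outcome needs bands that cover every possible score once. It also needs a stated relation to the diagnosis if it is called severity of that diagnosis. Neither condition is met.

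The moderate band stops at 14 and the severe band starts above 15, so the score between them is unassigned. It lies at the boundary that matters most clinically and where cases are likely to be few. Separately, presence of PTS and severity of PTS rest on different rules, and nothing in the article links them.

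At stake is the table for the first secondary aim. Whoever builds it must decide where a score of 15 goes, where a diagnosed patient scoring below 5 goes, and whether a score of 5 or more in an undiagnosed patient counts. Those decisions should be written down before the data are seen by arm.

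**Working it through.** **1. Coverage of the bands.** The rule as printed was applied to every whole-number score. The article gives 5 + 6 = 11 items but not the item scoring, so 0–3 per item (total 0–33) is an assumption. With item maxima of 2, 3 or 4 the total runs to 22, 33 or 44, and the result at 15 is the same.

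| Score | No ulcer, as printed | No ulcer, severe = 15 or more |
|---|---|---|
| 0–4 | no grade | no grade |
| 5–9 | mild | mild |
| 10–14 | moderate | moderate |
| 15 | **no grade** | severe |
| 16 and above | severe | severe |

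With an ulcer, scores 5–14 meet both a lower band and the severe rule. This resolves if the ulcer criterion overrides.

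The sign is unlikely to be a loss in text extraction, because the at-least sign is preserved several times in the same section (symptom duration, time since DVT, transfused units).

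**2. Diagnosis against grade.** The two rules side by side:

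| | Villalta below 5, no ulcer | Villalta 5 or more, or ulcer |
|---|---|---|
| Meets pain-and-swelling rule | primary event, no grade | primary event, graded (except 15 without ulcer) |
| Does not meet it | no event, no grade | no event, yet the bands call it PTS (same exception) |

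The top-left cell can occur. Suppose that pain and swelling are each one scored item and that nothing else scores. The combinations totalling below 5 are then:

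- ratings 1–2: 4 of 4;
- ratings 1–3: 6 of 9, namely (1,1), (1,2), (1,3), (2,1), (2,2), (3,1);
- ratings 1–4: the same 6, of 16.

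These counts show only that the cell is reachable. They are not frequencies, and the item list is itself an assumption. Mild + moderate + severe therefore need not equal the number of primary events.

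**3. Scale of the gap at 15.** Planning rates (*Sample size and power calculations*): 20% and 30%, taken here with 300 evaluable per arm.

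- Expected PTS: 300 × 0.20 + 300 × 0.30 = 60 + 90 = 150.
- The *Background* puts severe PTS at 1/4 to 1/3 of cases: 150/4 = 37.5 to 150/3 = 50.
- One patient scoring 15 equals 1/50 = 2.0% to 1/37.5 = 2.7% of that count.

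How many patients would score 15 is not derivable from the article.

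**4. Sample size, for completeness.** Pooled formula, two-sided 0.05, 80% power: n = [1.96·√(2·0.25·0.75) + 0.842·√(0.21 + 0.16)]² / 0.10² ≈ 294 per arm, 588 in total. The stated 600 is within about 2% of this, and 600/0.75 = 800 as stated. None of it uses the Villalta bands.

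**The case against.** The strongest reply is that this is one mistyped boundary on a cited scale, in a secondary outcome whose differences are only explored. Diagnosing with one instrument and grading with another is a legitimate choice. If grading is understood to apply only to diagnosed PTS, an undiagnosed patient scoring 5 or more is simply not a case, and that conflict disappears. Much of this stands: the gap is one value, probably a slip, and no effect on results can be shown. But the boundary is still printed wrongly, and on that same reading a diagnosed patient scoring below 5 still has no grade.

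A reader might infer three stronger things, and the article does not support them.

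- **That severity cannot be tabulated.** It can, once two short rules are added. The biomarker regression on the Villalta scale is also untouched by the gap at 15.
- **That the arms will be compared only among diagnosed patients, conditioning on the primary outcome.** The article never says so. Intention-to-treat covers all outcomes, and severity is described as rates in the two intervention groups.
- **That worsening after diagnosis is lost, because** "Patients diagnosed with PTS will be considered to have reached the study endpoint". That sentence classifies an event. *Study procedures* follows patients for 2 years with no stop at diagnosis. Table 1 schedules the follow-up form at 6, 12, 18 and 24 months, and that form includes PTS symptoms and signs. Venous ulcer is also compared as an outcome of its own.

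**Conclusion.** The point holds as a definitional error with a small, avoidable consequence. As printed, an ulcer-free Villalta score of exactly 15 has no grade, and neither does a diagnosed case scoring below 5. The grades therefore need not sum to the primary PTS count.

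The finding at 15 needs no assumption beyond whole-number scores that can reach 15. The finding below 5 rests on the absence of any Villalta threshold in the diagnostic rule. The number of patients affected is unknown. The 2–3% per patient depends on the planning event rates, 600 evaluable patients and the quoted share of severe cases. The primary outcome and the sample size are not affected. It should be corrected because it concerns the first secondary aim and the correction is trivial.

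**What to change.** Two changes of wording:

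1. Make the bands adjoin: mild 5–9, moderate 10–14, severe 15 or more or a venous ulcer, with the ulcer criterion overriding the score.
2. Report severity by arm with all randomised patients as the denominator, in four Villalta categories: below 5 without an ulcer, mild, moderate, severe. Each patient is then classified whatever the primary diagnosis. Add a note that these counts can differ from the primary PTS count; a cross-table of category by primary diagnosis would show where.

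Whether to use the worst or the final grade, whether to fit a proportional-odds model, and how to treat patients without a score are analysis choices that can be left to the SAP.

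The cost is a corrected threshold and one or two sentences, ideally before any comparison by arm. No new data are needed, because PTS symptoms and signs are already on the follow-up form, and the sample size does not change.

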### Sample size and power calculations

We hypothesized that event rates (i.e. PTS at 2 years) will be 30% in the inactive stocking vs. 20% in the active stocking group, i.e. a risk reduction of 33%. Our baseline event rate and effect size for the stocking group were based on a systematic review of available published data [68]. The total sample size required to detect this difference in event rates with a two-tailed α of 0.05 and 80% power is 600 [69]. We increased our sample size to 800 to take into account a projected 25% loss-to-follow up by 2 years.

For the biomarker analyses, our sample size provides > 80% power to detect ORs of 0.5 or lower, or 2.0 or higher. Larger alternatives will be associated with increased power. With regard to inflammatory markers, the analysis will be largely exploratory, as this study will be among the first to provide prospective data on levels of markers of inflammation in patients with DVT and PTS. However, the study design provides power of at least 80% to detect differences on the order of 1/3 of a standard deviation or larger between initial values of inflammatory markers in the two allocation groups.

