#### Current trial design

The study is a randomized, allocation concealed, double-blind multicenter clinical trial with an intervention allocation ratio of 1:1 (figure 1 summarizes the study design). Once a patient is deemed eligible and consents to the study, the research nurse at each site logs onto a web-based interface which allocates the patient to one of 2 treatment groups: active stockings or inactive (placebo) stockings. Treatment group is assigned randomly using permuted blocks of randomly varying sizes at each study site to maintain close balance of the numbers in each treatment group, at any time during the trial, and to ensure allocation concealment. The active stockings intervention consists of knee-length, 30–40 mm Hg (Class II), graduated ECS worn on the DVT-affected leg daily, applied upon waking and removed upon retiring, beginning as early as possible within 14 days after DVT diagnosis and continued for 2 years. The inactive stockings intervention (the control intervention) consists of knee-length, inactive stocking (5 mm Hg compression at ankle; similar to store bought trouser sock), identical in appearance to the active stockings, worn on the DVT-affected leg daily, applied upon waking and removed upon retiring, beginning as early as possible within 14 days weeks after DVT diagnosis, and continued for 2 years. Active and inactive stockings are manufactured by SIGVARIS Corp.

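### The blanket claim of more than 80% power for biomarker odds ratios of 0.5 or 2.0 does not hold for low-prevalence binary markers, and the 1/3-SD sentence names the wrong comparison

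*Protocol article*

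**What the plan says.** Protocol article, Sample size and power calculations: for the biomarker analyses, "our sample size provides > 80% power to detect ORs of 0.5 or lower, or 2.0 or higher". No marker prevalence is given. For the primary outcome, the event rates "will be 30% in the inactive stocking vs. 20% in the active stocking group", the total required "with a two-tailed α of 0.05 and 80% power is 600", and then "We increased our sample size to 800 to take into account a projected 25% loss-to-follow up by 2 years".

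The same section calls the inflammatory-marker analysis largely exploratory. It then claims at least 80% power for "differences on the order of 1/3 of a standard deviation or larger between initial values of inflammatory markers in the two allocation groups".

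Statistical analysis: "Factor VIII, D-dimer and markers of inflammation will be analyzed both as continuous data and as proportion of values exceeding the upper" 90th percentile. The distribution that supplies the percentile is not named. Binary markers are tested against PTS by chi-square, continuous ones by t-test, and both then enter logistic regression with PTS as the outcome. Aims of the study, secondary aim 5, likewise asks whether the markers influence the development and severity of PTS.

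**The concern.** Power to detect an odds ratio depends on the share of patients who carry the marker. A single figure for all biomarker analyses can be right only if it holds for the rarest split that is planned. A 90th-percentile split leaves a small exposed group, and a protective odds ratio is harder to detect there than a harmful one, because few events are expected among the exposed.

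The 1/3-SD sentence raises a different question. The baseline blood sample is taken at the enrollment visit, and stockings arrive a few days later (Table 1). Any difference in initial marker values between the stocking groups is therefore chance, and it says nothing about whether markers predict PTS.

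At stake is how the substudy's results can be interpreted. A reader who relies on the stated power would give a null finding on a 90th-percentile split more weight than it can bear.

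**Working it through.** **Inputs**
- Evaluable patients: 600, from 800 less 25% loss (Sample size and power calculations). All 800 is the best case.
- PTS: 30% and 20% in the two groups, with "double-blind multicenter clinical trial with an intervention allocation ratio of 1:1" (Current trial design), so (30% + 20%)/2 = 25% overall.
- Alpha: two-sided 0.05. It is stated for the primary outcome; the biomarker sentence gives none of its own.
- Exposed share: 10% for a 90th-percentile split. This assumes that the percentile is that of the study sample.

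**Reproducing the plan's primary figure**

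n per arm = [1.96·√(2·0.25·0.75) + 0.842·√(0.30·0.70 + 0.20·0.80)]² / 0.10² = (1.200 + 0.512)² / 0.01 ≈ 293.2, rounded up to 294. The total is 588 (626 with continuity correction). The stated 600 is consistent with this, and 600/(1 − 0.25) = 800. The primary calculation reproduces.

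**Power for the odds ratios**

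Let p1 and p0 be the PTS risks in exposed and unexposed patients. They solve:
- p1/(1 − p1) = OR · p0/(1 − p0)
- 0.10·p1 + 0.90·p0 = 0.25

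Power = Φ[(|p1 − p0| − 1.96·s0)/s1], where s0 = √[0.25·0.75·(1/n1 + 1/n0)] and s1 = √[p1(1 − p1)/n1 + p0(1 − p0)/n0].

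At N = 600, n1 = 60, n0 = 540 and s0 = 0.0589:
- OR 2.0: p1 = 38.1%, p0 = 23.5%, difference 0.1457, s1 = 0.0653. Φ[(0.1457 − 0.1155)/0.0653] = Φ(0.46) = **68%**.
- OR 0.5: p1 = 15.0%, p0 = 26.1%, difference 0.1109, s1 = 0.0498. Φ[(0.1109 − 0.1155)/0.0498] = Φ(−0.09) = **46%**.

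Simulating the chi-square test (200,000 runs) gives 67% and 48%, or 62% and 41% with continuity correction.

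At N = 800 with no loss, the same formula gives **79%** and **60%**.

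**By exposed share (N = 600, 25% PTS)**

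| Exposed | OR 2.0 | OR 0.5 |
|---|---|---|
| 5% (assumed, for illustration) | 45% | 23% |
| 10% | 68% | 46% |
| 15% | 80% | 64% |
| 20% | 87% | 77% |
| 25% | 91% | 84% |
| 50% | 95% | 95% |

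Power reaches 80% at about 15% exposed for OR 2.0 and about 22% for OR 0.5. At 10% exposed, the odds ratios detectable with 80% power are about 2.23 or 0.35 at N = 600, and about 2.02 or 0.41 at N = 800. Reaching 80% at 10% exposed would take about 821 evaluable patients for OR 2.0 and about 1,208 for OR 0.5.

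**Sensitivity at 10% exposed**
- N = 600, overall PTS from 20% to 40%: 64–72% for OR 2.0 and 38–65% for OR 0.5.
- N = 800, overall PTS 30%: 82% and 68%.
- N = 600, one-sided test, 25% PTS: 77% and 61%.

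OR 2.0 passes 80% only when all 800 are evaluable and either PTS is higher than planned or the test is one-sided (86%). OR 0.5 stays below 80% in every variant tried.

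**The 1/3-SD sentence**

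Power = Φ[(1/3)/√(1/n1 + 1/n2) − 1.96].
- By allocation, 300 vs 300: Φ(4.08 − 1.96) = 98%.
- With vs without PTS, 0.25·600 = 150 vs 450: Φ(3.54 − 1.96) = 94%.

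Both exceed the stated 80%. The number stands; the comparison named does not match the aim.

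**The case against.** The strongest reply is that the 10% exposed share is an assumption. The article names no reference distribution for the percentile. Its own background reports a median CRP of 37.5 in acute DVT against 5.0 in controls (with differing printed units), so a cut taken from controls could put far more than 10% of patients above it. From about 22% exposed the claim is met in both directions. This stands as a limit on the finding, but it does not rescue a sentence that carries no condition on prevalence.

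A reader might infer that the power claim is false for every biomarker. It is not. The same markers are also analysed as continuous data, where power is near 100% if the odds ratio is per SD. A pooled thrombophilia variable at one-third exposed would have 94% and 91% power. The article also gives no prevalence for any single polymorphism in its patients, so the 5% row is illustrative only.

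A reader might also infer that the 1/3-SD figure is miscalculated. It is not; only the named groups are wrong, and the aims and the analysis section describe the marker-versus-PTS comparison correctly.

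The largely exploratory label covers CRP, IL-6, IL-8 and MCP-1, which are most of the markers to be split. It weakens the point for those, but Factor VIII and D-dimer lie outside it.

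Finally, nothing in the article says that null results will be taken to exclude two-fold associations. That is a risk of the wording, not a stated intention.

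**Conclusion.** The concern holds in limited form. As a statement about all biomarker analyses, more than 80% power for odds ratios of 0.5 and 2.0 is not delivered. For a 90th-percentile split with about 10% exposed, power at the planned 600 evaluable patients is about 68% for OR 2.0 and 46% for OR 0.5. This rests on a study-sample percentile, 25% PTS overall, two-sided 0.05 and a crude comparison. The claim is sound for both odds ratios from about 22% exposed.

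The 1/3-SD sentence names a contrast that does not serve the biomarker aim, although its figure is correct for the contrast that does.

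The effect is confined to Bio-SOX, a secondary aim. It would be wrong to conclude that the trial's sample size or primary analysis is in question: the primary calculation reproduces and is untouched. This is a should-fix.

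**What to change.** 1. Replace the single power sentence with power by marker prevalence, stating N, overall PTS and alpha. Give the detectable odds ratios, for example about 2.23 or 0.35 at 10% exposed and N = 600. Limit the claim of more than 80% for both odds ratios to markers with a prevalence of about 22% or more.
2. State which distribution supplies the 90th percentile, since the power depends on it.
3. In the 1/3-SD sentence, replace the two allocation groups with patients with and without PTS (about 150 vs 450, 94% power). The figure of at least 80% can stay.

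The cost is wording and a few restated figures; the stated power for rare binary markers becomes less favourable. No change to the sample size, data collection or choice of main biomarker analysis is required. Making the percentile split descriptive only would be a preference, not a correction.
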